# Acceptability of the method of administration of a patient-reported outcome measure (PROM) with stroke survivors, a randomised controlled trial protocol

**DOI:** 10.1186/s13063-018-2694-4

**Published:** 2018-07-03

**Keywords:** Stroke, CVA, PROM, Questionnaire, Response rate, Online, Face-to-face, Postal, Telephone, Non-inferiority

## Abstract

**Background:**

UK-wide national clinical guidelines promote routine 6-month post-stroke follow-up assessment. However, as part of this 6-month assessment little information is gathered from the patient’s perspective. The means of collecting this patient-centred information might be served best by a patient-reported outcome measure (PROM) at the 6-month assessment time point. Currently, four different methods of 6-month follow-up assessment occur; the most common being face-to-face interview followed by telephone interview, postal questionnaire and online questionnaire. Therefore, this study will investigate if the acceptability of telephone, online or postal administration of a PROM at the 6-month post-stoke time point is not inferior to face-to-face administration.

**Methods/design:**

A UK multicentre, blinded (analyst and researcher), pragmatic, non-inferiority study, with 80% power using a 2.5% non-inferiority margin was designed to compare the acceptability of three modes of administration (telephone interview, postal questionnaire and online questionnaire) compared with face-to-face interview administration of a PROM. We plan to approach and randomise a minimum of 808 potentially eligible participants, 202 participants per group.

**Discussion:**

The aim of this ongoing research is to understand if there is a difference between face-to-face administration and the other three methods of administering a PROM as a patient-centred supplement to the 6-month review for stroke survivors. In utilising a pragmatic design, it is believed that this study will offer UK wide generalisable results, of the acceptability of the methods under investigation, to inform clinicians and commissioners of stroke services.

**Trials registration:**

ClinicalTrials.gov: NCT03177161. Registered on 6 June 2017.

**Electronic supplementary material:**

The online version of this article (10.1186/s13063-018-2694-4) contains supplementary material, which is available to authorized users.

## Background

Patient-reported outcome measures (PROMs) are standardised and validated questionnaires developed for the purpose of gathering outcome data from the patient’s perspective [1]. PROMs have come to play an increasingly important role in both clinical practice and research [2–5]. In the present clinical and research climate there are several generic (health condition non-specific) health-related quality-of-life measures available such as the EuroQol 5D (EQ-5D) [6] or the Short Form 36 (SF-36) [7]. These quality-of-life PROMs are currently used regularly in research studies to evaluate the effectiveness of interventions post stroke [8] and are integrated into healthcare systems for use in clinical settings [1].

However, there is currently no conclusive evidence regarding the best method of administration of a PROM with stroke survivors. Potential methods of administration include face-to-face, telephone, online and via the post. This choice of comparators is supported by the findings of the Sentinel Stroke National Audit Programme (SSNAP) [9], which found that all four methods of administration are utilised for 6-month post-stroke follow-ups, with face-to-face follow-up being the most common method.

PROMs response rates post stroke are mostly reported as secondary outcomes, in studies which concentrate on either the development of new PROMs or the reliability and/or validity of PROMs in specific conditions. In those studies that report response rate as a primary outcome, a large variability exists in the response rates reported from 70.1% [10] for a study by Lannin et al. (2013) comparing the cost-effectiveness of telephone vs mail methods of follow-up for the Australian National Stroke Registry to 45% [11] for a study by Duncan et al. (2005) examining response rate for the Stroke Impact Scale [12] when administered via mail or telephone methods in veterans. Recently, a cohort study conducted in the London area by Peters et al. (2014) examining PROMs collection by post, in primary care, for those with a long-term condition, received a response rate of 36.4% [13] for stroke survivors. Thus, with large levels of variability in response rates of previous studies this study has opted for a pragmatic design across a large number of research sites covering rural and urban populations.

The PROM to be utilised in this study is the Patient-reported Outcomes Measurement Information System 10 questions (PROMIS-10 Global Health) [14]. This PROM is recommended by the International Consortium of Health Outcomes Measurement (ICHOM) as part of a proposed standard set of minimum outcome data for stroke survivors developed by a global team of stroke specialists [15, 16]. However, the Stroke Standard Set working group proposes the inclusion of extra patient-facing health status questions. The first addition are three questions relating to ambulation, toileting and dressing that have been adopted from the RiksStroke (The National Quality Register for Stroke – Sweden) [17, 18]. Additionally, two further questions on feeding and communication were developed [15] by the ICHOM working group for stroke for simple yes/no responses. The 10 question in PROMIS-10 and separately the three questions from the RiksStroke and two questions from the ICHOM Stroke Standard Set will be utilised for this study. This group of 15 questions will, for ease of reference, be referred to as Patient-reported Health Status Questions (PRHSQs).

Therefore, the objective of this research study is to provide an evidence base for the acceptability of modes of administration of the PROMIS-10 and five additional questions for stroke survivors, and to evaluate if online, postal and telephone modes are not inferior to face-to-face administration.

## Methods/design

### Study design

This study is a UK four- arm, pragmatic, multicentre, non-inferiority randomised controlled trial of the method of administering the PRHSQs at the 6-month post-stroke time point (clinically confirmed stroke diagnosis ≥ 4 months to ≤ 8 months). The ratio of allocation is 1:1:1:1, with face-to-face being the method of administration against which the non-inferiority of the three comparator methods (online, postal and telephone) will be discerned. Participants will be randomly allocated to one of four methods of administering these 15 Patient-reported Health Status Questions at eligibility and asked to consent via the post. By virtue of the fact that any of the four methods under investigation are established practices in UK stroke services, participants will not be informed about the other possible modes of administration. Addressing this research question requires implementation of a Zelen design [19] this acknowledges the issues of contacting patients prior to obtaining consent. The impact of this design is due to the nature of the intervention, approaching participants later than usual, as well as a larger-than-usual sample size. We acknowledge that informing participants of the alternative methods of administration may introduce bias, as the rate of return of the PRHSQs for the different assessment methods is the primary outcome of interest. Therefore, participants will knowingly consent to receive and complete the PRHSQs via a single method of administration. See Fig. 1 for the participant flow diagram The study protocol was written in full compliance with the Standard Protocol Items: Recommendations for Interventional Trials (SPIRIT) 2013 [20] and a completed SPIRIT Checklist and Figure 2013 (Fig. 2) [21] are available as a supplement (Additional file 1).

**Fig. 1 Fig1:**
[figure not shown]
Participant flow diagram

**Fig. 2 Fig2:**
[figure not shown]
Standard Protocol Items: Recommendations for Interventional Trials (SPIRIT) Figure

### Recruitment

The study has gained acceptance by the Health and Care Research Wales (HCRW) Clinical Research Portfolio, thereby allowing for National Health Service (NHS) organisations in all four devolved nations, via the UK Clinical Research Network Portfolio of studies, to view the basic study design and to approach the central research team for permission to open as a research site and conduct the research. The researchers will conduct an open-door policy and will offer the study to any capable NHS organisation who expresses an interest, based on the following site inclusion criteria: (1) patients who meet the study inclusion criteria are routinely under the care of the principle investigator (PI) at the research site and (2) the research site is able to facilitate all four arms of the study.

### Study setting

The study will be undertaken in 14 centres across England and Wales. Centres acting as research sites will be those who were previously involved in potentially eligible participants’ post stroke care. In line with the time-frame of the study, the majority of potentially eligible participants will reside in the community and will be anticipating routine clinical follow-up from the centres acting as research sites.

### Study population; inclusion and exclusion criteria –

#### Inclusion

Clinically confirmed diagnosis of stroke either Cerebral Infarct (ICD I63), Cerebrovascular Haemorrhage (ICD I61) or Stroke, not specified as haemorrhage or infarction (ICD I64) [22]Patients aged ≥ 18 yearsReceived a clinically confirmed diagnosis of stroke within the last 4–8 months (stroke diagnosis ≥ 4 months to ≤ 8 months)

#### Exclusion

Clinically confirmed diagnosis of a Transient Ischaemic Attack (ICD G45) [22]Clinically confirmed diagnosis of a Subarachnoid Haemorrhage (ICD I60) [22]

### Sample size

Using a non-inferiority margin of 2.5%, with a power of 80% and 2.5% significance level and expecting the same response rate in each group, a minimum of 202 patients are required per randomised allocation group. Thus, a minimum total of 808 randomised eligible participants are necessary for statistical analysis. No adjustment will be made for carrying out three pair-wise tests. Secondary outcomes may not necessarily be powered.

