### Statistical analysis

#### Analysis of the primary outcome

We will carry out a difference of two proportions between the three intervention groups (postal, telephone or online) verses face-to-face administration, with a 2.5% non-inferiority margin. The three comparisons will be adjusted using a Holm [24] multiplicity adjustment, with a two-sided alpha = 0.05. The analysis will be presented as a difference with an associated 95% confidence interval (CI).

Analyst and researchers blinding to the allocation will remain in place until interpretation of the primary and secondary outcomes are agreed. Following un-blinding of the allocation, difference will be generated in the three comparator allocation groups, and face-to-face completion rate, and will include the non-inferiority margin of 2.5%, as our primary analysis.

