### Non-inferiority margin

Utilising unpublished routinely collected clinical data approximately 85% of follow-up appointments for all patients, who would meet the inclusion criteria, return for face-to-face administration of their 6-month post-stroke follow-up assessment at the ≥ 4-month to ≤ 8-months post-diagnosis time point. The reason for this high level of face-to-face follow-up is not grounded on evidence, however, disability and communication issues post stroke may have a role in the choice of this method. Nevertheless, there is a significant cost implication in the choice of method for follow-up as evidenced in a study by Lannin et al. (2013) investigating the cost-effectiveness of telephone vs mail methods of follow-up for the Australian National Stroke Registry [10].

Alongside the National Institute for Health and Care Excellence (NICE) accredited RCP stroke guidelines [25], a non-inferiority margin of 2.5% was decided upon as the maximum tolerated acceptable reduction in acceptability, alongside conflicting resource allocation and offering flexibility of patients to undergo follow-up.

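### With a 2.5-point non-inferiority margin, 202 per arm does not give the stated 80% power at any response rate in the protocol; it gives about 7–10% unadjusted and about 4–5% with Holm

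*Protocol article*

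**What the plan says.** The Sample size section gives its inputs as "Using a non-inferiority margin of 2.5%, with a power of 80% and 2.5% significance level and expecting the same response rate in each group" and concludes that "a minimum of 202 patients are required per randomised allocation group", so that "a minimum total of 808 randomised eligible participants are necessary for statistical analysis". It also says that the three pairwise tests will not be adjusted. The abstract describes the trial as one "with 80% power using a 2.5% non-inferiority margin was designed to compare the acceptability" of the modes.

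The margin is the same throughout. The Non-inferiority margin section says that "a non-inferiority margin of 2.5% was decided upon as the maximum tolerated acceptable reduction in acceptability", and the primary analysis tests a difference of two proportions against 2.5%. That analysis applies Holm to the three comparisons "with a two-sided alpha = 0.05" and reports a 95% confidence interval.

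The Sample size section states no response rate. The Non-inferiority margin section says that "approximately 85% of follow-up appointments for all patients, who would meet the inclusion criteria, return for face-to-face administration", from unpublished routine data. The Background cites response rates of 70.1%, 45% and 36.4% from earlier studies.

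**The concern.** A margin of 2.5 points on a difference of two proportions is narrow, and 202 per arm is small for it. Unless the common response rate is close to 0% or 100%, the confidence interval will be several times wider than the margin. Two modes that are truly equal would then usually fail the test.

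The results are meant to inform clinicians and commissioners. A reader told that the trial has 80% power may take a failure to show non-inferiority as informative about telephone, postal or online administration, when the design could seldom have shown non-inferiority at all.

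**Working it through.** **Inputs.** Margin d = 0.025 (abstract, Sample size, primary analysis and margin sections). Significance level 2.5%, read as one-sided, which matches the two-sided 0.05 and 95% interval of the analysis section. Power 80%. True difference 0. Equal arms: "The ratio of allocation is 1:1:1:1". n = 202 per arm. Common rate p: not stated, so 85% from the margin section and 70.1%, 45% and 36.4% from the Background are tried in turn.

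**Required size.** n = (1.960 + 0.842)² × 2p(1 − p) / d², with (1.960 + 0.842)² ≈ 7.849.

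At p = 0.85: 7.849 × 0.255 / 0.000625 = 3,202.3, so 3,203 per arm. The stated 202 is not reproduced.

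**Power at 202.** SE = √(2p(1 − p)/202); power = Φ(d/SE − 1.960).

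At p = 0.85: SE = √(0.255/202) = 0.0355, and Φ(0.7036 − 1.960) = Φ(−1.256) = 0.104. Exact binomial calculation gives 10.6% with a Wald interval and 10.4% with the Farrington–Manning test.

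| Common rate | n per arm for 80% power | Power at 202, unadjusted | Average power per comparison, Holm | 95% CI half-width at 202 |
|---|---|---|---|---|
| 85% | 3,203 | 10.4% | about 5.3% | ±7.0 points |
| 70.1% | 5,265 | 7.9% | about 3.7% | ±8.9 points |
| 45% | 6,217 | 7.3% | about 3.5% | ±9.7 points |
| 36.4% | 5,815 | 7.5% | about 3.5% | ±9.4 points |

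The half-width is 1.96 × SE. The Holm column comes from simulation: 400,000 trials, four arms with equal true rates, shared face-to-face arm, one-sided family level 0.025. At 85%, all three equal modes pass in about 1.5% of trials without adjustment and about 1.2% with Holm. At least one passes in about 24% and 11% respectively.

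**Observed advantage needed.** At 85% and unadjusted, the lower limit clears −2.5 points only if the mode is observed at least about 7.0 − 2.5 = 4.5 points better than face-to-face.

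**Other readings of the inputs, at 85%.**
- One-sided 5%: 2,523 per arm.
- 2.5% two-sided: 3,879.
- Continuity correction: about 3,283.
- Margin taken as 2.5% of 85%: 4,433.
- Superiority formula for 85% against 82.5%: 3,418.

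None is near 202.

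**What would give 202.** With d = 0.025, solving for p gives about 99.2% (or 0.8%). With p = 0.85, solving for the margin gives 9.95 points; a 10-point margin gives 7.849 × 0.255 / 0.01 = 200.1, so 201 per arm. Neither the 99.2% rate nor a 10-point margin is in the article.

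**The case against.** An article may leave the assumed response rate to the full protocol, and 85% is not presented as the planning rate. It describes routine attendance. The primary outcome counts questionnaires returned among all eligible people, and those who do not return a postal consent form never receive one. So 3,203 and 10% are conditional on a rate that the Sample size section does not claim. That stands, and it is why the figures are given as a range. It does not rescue 202: an omitted rate would have to be about 99.2%. Needing consent as well as completion makes a rate below 85% plausible, and at the cited lower rates power is worse.

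The unadjusted 7–10% is also not the power of the planned primary analysis, which uses Holm. That stands too, so both sets of figures are needed until the two sections agree.

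Three stronger readings are tempting but unsupported:
- A reader might infer that the calculation used a 10-point margin. The numerical fit is close, but the article never mentions such a margin.
- A reader might infer that the trial is almost certain to show nothing. Without adjustment, and with equal rates of 85%, at least one mode passes in about 24% of trials. Very probably inconclusive for a given mode is as far as the figures go.
- A reader might infer that an inconclusive result will be reported as inferiority. The article plans differences with confidence intervals and adherence to the CONSORT non-inferiority extension, so misreading is a risk and not something the plan proposes.

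**Conclusion.** The stated power is wrong as written. With a 2.5-point margin, a one-sided 2.5% level and equal true rates, 202 per arm gives 7.3% to 10.4% power per comparison at the rates in the article, or about 3.5% to 5.3% on average with Holm, against the claimed 80%. Reaching 80% unadjusted would take 3,203 to 6,217 per arm, about 16 to 31 times the planned number (3,203/202 and 6,217/202).

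This assumes an absolute margin, as the difference-of-proportions analysis implies, and equal true rates, as the plan states. The conclusion does not depend on choosing 85%: even a common rate of 95% would need 1,194 per arm and give 21% power unadjusted. How the 202 arose cannot be settled from the article.

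**What to change.** Correct the Sample size section and the abstract:

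1. State the assumed response rate for the primary outcome itself, meaning postal consent and questionnaire completion among all randomised.
2. Reconcile the Sample size section (no adjustment) with the primary analysis (Holm).
3. Restate the power at 202 per arm for the 2.5-point margin: about 7–10% per comparison unadjusted, or about 4–5% on average with Holm, according to the rate and the rule chosen.
4. If the calculation used a different margin, say so and reconcile it with the abstract, the primary analysis and the margin section.
5. Give the expected 95% CI half-width (about ±7 to ±10 points), and say that failure to exclude −2.5 points will be reported as inconclusive.

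The cost is wording and a much less favourable power statement. Recruitment was planned to end in February 2018, before the article appeared in July 2018. The realistic step is therefore a transparent correction; it requires no additional enrolment.

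### The protocol gives opposite multiplicity rules for the three primary comparisons: no adjustment under Sample size, Holm under Analysis of the primary outcome

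*Protocol article*

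**What the plan says.** The design compares three modes (online, postal, telephone) with one shared face-to-face group: "The ratio of allocation is 1:1:1:1, with face-to-face being the method of administration against which the non-inferiority" of the other three is judged (Study design).

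Two sections of the protocol article address multiplicity for these comparisons:

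- Sample size: "No adjustment will be made for carrying out three pair-wise tests". The calculation is described as "Using a non-inferiority margin of 2.5%, with a power of 80% and 2.5% significance level", and then "expecting the same response rate in each group, a minimum of 202 patients are required per randomised allocation group".
- Analysis of the primary outcome: "The three comparisons will be adjusted using a Holm [24] multiplicity adjustment, with a two-sided alpha = 0.05". Each result is to be shown as a difference with a 95% confidence interval.

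Both are current text. No sentence limits the first to the sample-size calculation or says that the second overrides it.

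**The concern.** Read as written, the two statements cannot both hold for the same three tests. One lets each mode be judged at one-sided 2.5%. The other requires the strongest result to pass 0.83% before anything can be claimed. The same data could then support a non-inferiority claim under one section and no claim under the other.

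This is the confirmatory rule for the primary outcome, and the Abstract says the results are meant to inform clinicians and commissioners. If no adjustment were made, the chance of at least one false non-inferiority claim would exceed the nominal 2.5%. If Holm is used, the stated sample size and power do not describe the analysis that will be run.

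**Working it through.** **Inputs.** Margin 2.5 points, power 80%, 2.5% significance level (read as one-sided), equal true rates, 202 per arm (all Sample size); Holm at two-sided 0.05, that is one-sided 2.5% for non-inferiority (Analysis of the primary outcome); equal allocation with a shared control (Study design). The Sample size section gives no planning rate. I assume 85%, the face-to-face return figure under Non-inferiority margin ("Utilising unpublished routinely collected clinical data approximately 85% of follow-up appointments for all patients"), and show other rates below.

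**1. The plan's own figure.** n per arm = (z₁₋α + z₀.₈)² × 2p(1−p) / margin² = (1.960 + 0.842)² × 0.255 / 0.000625, giving 3,203. The stated 202 does not reproduce. That is a different defect and is not counted here; it matters only for reading the power figures in step 6.

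**2. Holm thresholds.** One-sided 0.025/3 = 0.0083, 0.025/2 = 0.0125 and 0.025/1 = 0.025, with z = 2.394, 2.241 and 1.960. The matching two-sided interval levels are 98.3%, 97.5% and 95%.

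**3. Family-wise error.** With all three modes exactly at the margin, the shared control and equal arms give correlation 0.5 between the test statistics.
- Unadjusted: 1 − Φ₃(1.96, 1.96, 1.96; 0.5) = 6.3%. Were the tests independent, it would be 1 − 0.975³ = 7.3%.
- Holm: about 2.2% by simulation.

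**4. Observed difference needed at 202 per arm, 85%.** SE = √(0.255/202) = 3.55 points.
- Unadjusted: 1.960 × 3.55 − 2.5 = about +4.5 points.
- Holm, second step: 2.241 × 3.55 − 2.5 = about +5.5 points.
- Holm, first step: 2.394 × 3.55 − 2.5 = about +6.0 points.

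**5. How often the rules differ.** Simulation with 202 per arm, equal true rates and a shared control. The last column is the share of trials in which the two rules declare a different number of modes non-inferior.

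| Assumed rate | Rules differ |
|---|---|
| 85% | about 14% |
| 70% | about 11% |
| 50% | about 10% |

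The response rates cited in the Background run from 36.4% to 70.1%. Their p(1−p) lies between about 0.21 (70.1%) and 0.2475 (45%), so the 50% and 70% rows cover them. At 85%, about 12% of all trials have at least one mode passing unadjusted while Holm declares none.

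**6. Power per comparison at 202 per arm.** Power = Φ(margin/SE − z₁₋α).
- 85%: 2.5/3.55 = 0.704. Unadjusted Φ(0.704 − 1.960) = 10.4%; first Holm step Φ(0.704 − 2.394) = 4.5%. Averaged over the three comparisons, full Holm gives about 5.2% by simulation.
- At the Background rates (36.4%, 45%, 70.1%): 7.3% to 7.9% unadjusted, about 3% at the first Holm step.

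**7. Cost of multiplicity in sample size, at 85%.** At α = 0.0083: (2.394 + 0.842)² × 0.255 / 0.000625, giving 4,272 against 3,203 unadjusted, a ratio of 1.33. This sizes for the first step only and so overstates what Holm needs. At 3,203 per arm, power at 0.025/3 is about 66%, while simulated Holm power per comparison is about 74%.

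**The case against.** The strongest reply is that the sample-size sentence sits between the total N and a remark about power for secondary outcomes. It may therefore mean only that N was not inflated for three tests. The analysis section governs the primary analysis, and it names one procedure, its alpha and the margin. That is a fair reading, and it is why the fix keeps Holm. It does not remove the problem: the sentence speaks of making no adjustment for tests, does not confine itself to N, and on this reading the sizing still does not match the analysis.

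Four stronger inferences are tempting, and the document does not support them.

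- *The success rule is undefined.* It is not. Holm is named in the governing section, so the rule is contradicted elsewhere and thereby ambiguous.
- *The 95% interval is a competing decision rule.* The protocol says only this: "The analysis will be presented as a difference with an associated 95% confidence interval (CI". It never says that non-inferiority is read from that interval, and unadjusted intervals shown beside adjusted tests are common. Since they do not match Holm's first two steps, a label is worth adding, but this is secondary.
- *The two alphas conflict.* One-sided 2.5% and two-sided 5% agree for a non-inferiority test.
- *Multiplicity explains the low power.* Unadjusted power at 85% is already 10.4%. Multiplicity accounts for the step from there to 4.5%; the rest comes from 202 not following from a 2.5-point margin.

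On choosing the rule after seeing results: analysts and researchers stay blinded to allocation until interpretation is agreed. That reduces the opportunity without settling which rule applies.

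**Conclusion.** The point stands as a contradiction between two sections on the multiplicity rule for the primary claim, and the sections must be reconciled. Its size is a family-wise one-sided error of about 6.3% instead of 2.5% if no adjustment is made, and a different count of non-inferior modes in roughly one simulated trial in seven at 85%, or one in ten to one in nine at 50–70%.

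The 6.3% assumes large-sample normality, equal arms and all three modes at the margin; it does not depend on the return rate. The disagreement figures assume 202 per arm and equal true rates. The 85% is an assumption, since no planning rate is stated.

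**What to change.** - Keep Holm as the single rule, as the analysis section already specifies.
- Reword the sample-size sentence, without simply deleting it: the sample size was not inflated for multiplicity, and the primary tests are Holm-adjusted. Deletion would lose a useful disclosure if that is what was meant.
- State in Analysis of the primary outcome that each non-inferiority claim rests on the Holm-adjusted one-sided p-value against the 2.5-point margin, at family-wise 2.5%.
- Label the 95% intervals as descriptive, or use Holm-compatible bounds. Fixed 98.3% limits would not do: they are Bonferroni intervals, and at 85% with 202 per arm they contradict Holm for at least one mode in about 14% of simulated trials with any Holm success.
- Restate power under Holm, giving power at 0.025/3 as a lower bound.

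The cost is a few sentences and a rerun of the power calculation, with no change to conduct or data collection. The rewording should be settled before allocation is unblinded. The downside is that stated power per comparison falls below the unadjusted figure.
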